#### Secondary outcome

Percentage of LOS longer than the threshold corresponding to the 98^th^ percentile of the distributionPost-operative quality of recovery score, measured with the QoR-15 [16] questionnaire around 24 hours after surgeryIncidence of post-surgical complications, defined according to the Clavien-Dindo classification [19]Intensive care unit access in the post-operative periodPercentage of Emergency Department (ED) admissions up to 30 days after surgery (regardless of diagnosis)Percentage of readmissions to hospital within 30 days after surgery (regardless of diagnosis)Percentage of re-intervention (within 30 days after surgery)Perceived patient satisfaction score measured with the SSQ-8 [20] questionnaire via telephone interview around two weeks after discharge (only in a random sub-sample of patients keen to participate)Average healthcare costs, calculated from pre-hospitalization up to 30 days after surgeryAssessment of professionals’ satisfaction measured qualitatively.

#### Data collection

The CRF is available in a dedicated area of the EPICLIN electronic platform. EPICLIN is developed and managed by the Clinical Epidemiology Unit, compliant with all the security requirements of the General Data Protection Regulation (EU regulation 2016/679). Data related to the peri-operative care are prospectively and uniformly collected in the database during the entire by the local ERAS team. The post-operative recovery will be measured at 24 hours after the intervention through the QoR-15 questionnaire (available and validated in English) [16] and translated in Italian.

Patients’ satisfaction is measured through the SSQ-8 questionnaire, available and validated in English [20] (and translated in Italian), administered by trained staff to a sample of patients (or alternatively their caregivers) during a telephone interview two weeks after discharge.

At the end of the study health professionals’ satisfaction will be assessed qualitatively through questionnaires and focus groups.

Healthcare costs incurred between the first pre-admission visit and 30 days after hospital discharge, will be evaluated including the following categories of resources: pre-intervention visits, hospital stay days (including intensive care days), type of intervention, treatment of complications, re-interventions, ED access, new hospitalizations.

Further details on data collection are reported in the Supporting Information (see section “Data collection” in S1 File).

*Patient and Public Involvement*: No patient involved.

### Statistical plan

Fig 1 describes the sequence of randomizations of the clusters with the number of centers and the expected patients for the control and experimental periods. The total number of cases expected in 15 months is around 2400 patients (about 200 cases in the control period and 1200 in the experimental period).

Details on sample size estimation and power assessment are reported in the Supporting Information (see section “Statistical plan” in S1 File).

The main end-point, mean LOS calculated after excluding the durations greater than the threshold, will be compared between the two study periods using a random-effect linear regression model, adjusting for the time effect and the surgical technique (laparoscopic vs. open surgery). The center will be included in the model as a random effect. For dichotomous endpoints measured as proportions (e.g. length of stay above the threshold, complications, readmissions), the effect of implementing the ERAS protocol will be estimated with logistic regression models, with centers as random effects, including in the model the same set of covariates used for the analysis of the LOS.

Details on subgroup analyses and sensitivity analyses are provided in the Supporting Information (see section “Statistical plan” in S1 File).

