**Methods:**

The study protocol provides for a multicenter stepped wedge cluster randomized trial, focused on women undergoing an hysterectomy, for comparison between standard perioperative management and perioperative management according to the ERAS protocol. The primary outcome is the length of hospital stay (LOS). Secondary outcomes are: post-operative complications, quality-of-recovery at 24-hours after surgery, 30-day readmissions, patients’ satisfaction, healthcare costs. The compliance to all the ERAS items is monitored with an A&F approach. All the gynecologic units of Piedmont hospitals are involved and all the patients hospitalized for elective hysterectomy in the period of the study are included. Centers, stratified by surgical volume and randomly assigned to four groups, are randomly ordered to activate the ERAS protocol in four periods, every three months. The planned calendar and the total duration of the study have been extended for six months due to the COVID-19 pandemic. The expected sample size of about 2400 patients has a high statistical power (99%) to detect a reduction of LOS of 1 day (effect size 0.5) and to estimate clinically meaningful changes in the other study endpoints. The study protocol has been approved by the Ethical Committee of all participating centers. Study results will be timely circulated within the hospital network and published in peer-reviewed journals.

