### Stratification and randomization of the centers

All the gynecologic units were contacted prior to the beginning of the study to assess their level of knowledge of the ERAS protocol. Centers which already had fully adopted the protocol before the start of the study were excluded from randomization and included in an observational group to serve as an external benchmark for the study. All the other centers were stratified by the volume of hysterectomies performed during 2018 and randomly divided into 4 groups, each with a similar number of units and procedures. Then, the 4 groups were randomly ordered to activate the protocol according to a predefined calendar with 3 months interval between successive rounds. This stratified randomization was adopted to assure a more homogeneous composition of the groups for each activation period. All randomization procedures were performed by the Clinical Epidemiology unit after anonymizing the centers. The calendar date for protocol activation was communicated to each group about two months before the starting date to allow sufficient time for the training of the local ERAS team and to organize the activity.

After an initial 3-months period of data collection, performed in all centers to describe the baseline usual care, the first group of hospitals activates the ERAS protocol and then, every three months, the other groups follow step by step.

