## Discussion

This paper presents the study protocol of a stepped wedge cluster randomized controlled trial aimed to estimate the impact of a quality improvement intervention (the adoption of the ERAS protocol for hysterectomy in the entire regional hospital network in Piedmont). In 2017 an international survey [17] and a regional survey assessed that only few selected hospitals were compliant with the ERAS protocol in gynecologic surgery. Among the reasons for this limited uptake were the scarce diffusion of the multidisciplinary management of the patient and the lack of an organization that could enable the full adoption of the protocol, as a bundle, to obtain the desired positive effects.

To overcome the usual barriers to innovation in health care, especially at the organization level, and to monitor the changes in terms of appropriateness and safety, a structured Audit and Feedback (A&F) strategy has been planned in parallel to the trial. Even if the use of A&F is strongly recommended within the ERAS protocol, it is unusual that this strategy is carefully designed and conducted according to the best practice guidelines [21].

The “stepped wedge cluster randomized trial” study design has several advantages and some limits. Randomization at patient level would not be feasible due to the organizational nature of the intervention requiring a modification of the care process at center level. However, compared to other study designs, such as a before-after cluster randomized trial, the stepped wedge has a lower risk of bias due to possible confounding time effect and a complete coverage of the participating centers at the end of the study. This last advantage could theoretically represent even a risk in the unlikely, but not impossible, scenario of a disappointing effect of the experimental intervention.

Due to COVID-19 pandemic, the ERAS protocol was only partially implemented by some centers due to the shortage of staff and several organizational drawbacks. The extension of the study duration was intended to allow the centers, especially those in the third and fourth groups, to consolidate the implementation of the ERAS items. Such extension has also the purpose to get a sufficient sample size for the planned analyses on the secondary endpoints, counterbalancing the activity reduction (mainly among benign cases) registered during the pandemic.

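### The length-of-stay model has centre as its only random effect, so its standard error will be too small if centres drift apart over time, which the pandemic makes plausible but not certain

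*Protocol article*

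**What the plan says.** The Statistical plan section of the protocol article compares mean LOS between the control and ERAS periods "using a random-effect linear regression model, adjusting for the time effect and the surgical technique (laparoscopic vs. open surgery", and adds: "The center will be included in the model as a random effect". Binary outcomes use "logistic regression models, with centers as random effects, including in the model the same set of covariates used for the analysis of the LOS". The text shown names no centre-by-period term, no correlation that decays with time and no ERAS effect varying by centre. The section refers to the supporting file for sample size, subgroup and sensitivity analyses, but states the main models itself.

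The Discussion reports that "Due to COVID-19 pandemic, the ERAS protocol was only partially implemented by some centers due to the shortage of staff". It also says that activity fell during the pandemic, mainly among benign cases. Trial status records a six-month extension of the timetable.

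**The concern.** The article fixes a correlation structure, so this is a stated choice and not a detail left open. A centre intercept plus a common time effect makes two assumptions. Within-centre correlation is the same whatever the time between two operations, and no centre departs from the shared time trend.

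In a stepped wedge the ERAS effect is estimated largely from change within centres over time. If one centre's LOS shifts in a given quarter for its own reasons, the shift enters the effect estimate, but this model has no term that carries it into the standard error.

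The article gives trial-specific reasons to doubt the assumptions. Staff shortages affected some centres and not others. Case mix moved away from benign disease, and benign or malignant status is not a named covariate. The study ran for longer than planned. At stake are the width of the confidence interval for LOS and the false-positive rate for modest LOS effects, with a similar but unquantified risk for the binary outcomes.

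**Working it through.** **1. The plan's own figure.** The abstract claims "high statistical power (99%) to detect a reduction of LOS of 1 day (effect size 0.5". Effect size 0.5 for 1 day implies SD = 1/0.5 = 2 days. With two-sided alpha 0.05 (assumed), a simple comparison of means needs 2 × ((1.960 + 2.326)/0.5)² = 147 per arm for 99% power. With 1200 per arm, power is above 99.99%. The figure is therefore reproduced in the sense that 99% is comfortably met. This says little about the correlation structure. The printed split ("around 2400 patients (about 200 cases in the control period and 1200 in the experimental period") does not add up to 2400. In a balanced wedge of 4 groups and 5 periods, 1 + 2 + 3 + 4 = 10 of 20 group-periods are control, so 1200 + 1200 is used here.

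**2. Inputs.**
- From the article: 2400 patients, SD 2 days (implied), 4 groups ("randomly divided into 4 groups, each with a similar number of units and procedures"), one baseline quarter and four steps, so 5 quarters.
- Assumed: K = 20 to 28 equal-sized centres (the number stands only in the figure, which is not shown), ICC 0.01 to 0.20, and autocorrelation (CAC, the ratio of between-quarter to within-quarter correlation) 0.8. The article gives no ICC or CAC.

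**3. Method.** Split the variance σ² = 4 into
- centre: ICC × CAC × σ²
- centre-by-quarter: ICC × (1 − CAC) × σ²
- residual: (1 − ICC) × σ²

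With m = 2400/(5K) patients per centre-quarter, the covariance of a centre's quarterly means is V = centre × J + (centre-by-quarter + residual/m) × I, where J is all ones and I is the identity. The stated model fits W, which has no centre-by-quarter part. W is taken at its limiting maximum-likelihood values. With X holding the quarter and ERAS indicators, and sums over centres:
- A = Σ X′W⁻¹X, and the model variance is A⁻¹
- B = Σ X′W⁻¹VW⁻¹X, and the true variance is A⁻¹BA⁻¹
- type I error = 2 × [1 − Φ(1.96 × SE_model/SE_true)]

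**4. One case in full.** K = 24, ICC 0.05, CAC 0.8, so m = 2400/120 = 20. Centre variance is 0.16, centre-by-quarter 0.04, residual 3.80. The non-shared variance of a quarterly mean is truly 0.04 + 3.80/20 = 0.23, against 0.19 without the centre-by-quarter part. A rough SE ratio is √(0.19/0.23) = 0.91. The full calculation gives SE_model 0.138, SE_true 0.149, ratio 0.921. Type I error = 2 × [1 − Φ(1.805)] = 7.1%.

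**5. Results at CAC 0.8.**

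| ICC | SE ratio, 20 centres | Type I, 20 centres | SE ratio, 28 centres | Type I, 28 centres |
|---|---|---|---|---|
| 0.01 | 0.983 | 5.4% | 0.988 | 5.3% |
| 0.05 | 0.906 | 7.6% | 0.933 | 6.8% |
| 0.10 | 0.822 | 10.7% | 0.867 | 8.9% |
| 0.20 | 0.692 | 17.5% | 0.754 | 13.9% |

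At CAC 1 the ratio is 1.000 and type I error 5.0% throughout.

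**6. Simulation check.** REML fits of the stated model (24 centres, 2000 trials per scenario) gave 5.1%, 7.2% and 9.9% at ICC 0.05 for CAC 1, 0.8 and 0.6. At ICC 0.10 they gave 7.1%, 9.8% and 13.4% for CAC 0.9, 0.8 and 0.6.

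**7. Wider range and the extension.** For ICC 0.02 to 0.10, CAC 0.9 to 0.6 and 16 to 32 centres, type I error is 5.3 to 18.5% over 15 months. Over 21 months it is 5.2 to 14.4%, if the pause is assumed to fall before groups 3 and 4.

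**8. Consequence for effects of different size.** With a centre-by-quarter term the SE in the step 4 case is 0.149, and 1/0.149 − 1.96 = 4.75, so power for 1 day exceeds 99.99%. In the worst case of step 5 (20 centres, ICC 0.20) the SE is 0.1925 and power is Φ(1/0.1925 − 1.96) = Φ(3.23) = 99.9%. A small effect is different. An observed 0.28 day gives z = 0.28/0.138 = 2.03 under the stated model but 0.28/0.149 = 1.88 under the richer one, on opposite sides of 1.96.

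**The case against.** The strongest reply is that nothing in the article shows LOS trends diverging between centres. A pandemic shock shared by all centres goes into the time effect, and surgical technique is adjusted for. Partial implementation is, by itself, uneven delivery of ERAS. If ERAS has no effect, uneven delivery adds no variance and cannot raise type I error. All of this stands. A reader might infer that centre-by-period variation is certain. The article supports only that uneven staff shortages and a changing case mix make it plausible.

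A reader might also infer that type I error exceeds 5% for every binary outcome. That is not shown. No logistic model was simulated, and on a linear approximation inflation is negligible at low ICC: 5.1 to 5.2% at ICC 0.005 and CAC 0.8. LOS beyond the 98th percentile gives only about 0.02 × 2400 = 48 events, so a centre-by-quarter variance may not be estimable. Kenward-Roger and Satterthwaite corrections belong to linear mixed models and do not carry over directly to logistic ones.

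Finally, sensitivity analyses in the supporting file, which is not shown, may relax the structure. They may, but the primary p-value would still come from the model stated in the article. The absence of degrees-of-freedom or time-coding detail is not itself held against the plan.

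**Conclusion.** The point holds conditionally. If centre-by-period variation is present, the stated LOS model understates its standard error; if it is absent, the model is sound. Under the assumptions listed, the effect ranges from trivial at ICC 0.01 to serious at ICC 0.20, and the article does not allow one value to be chosen. The ICC, the autocorrelation, the number of centres and equal centre sizes are all assumed.

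The headline comparison is not endangered: a true 1-day reduction would be detected under either model. What is exposed is the interpretation of smaller LOS effects and the reported interval width. For binary outcomes the same direction is expected, but its size is unknown and may be small. This is a worthwhile, inexpensive improvement and not a flaw that invalidates the analysis.

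**What to change.** In the primary LOS model, add a centre-by-quarter random effect (or a correlation that decays with time between quarters) and use a small-sample degrees-of-freedom correction. Report the centre-only model, and a model with a random ERAS effect by centre, as sensitivity analyses.

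For the binary outcomes, where the plan says the effect "will be estimated with logistic regression models, with centers as random effects", add the centre-by-quarter term where event counts allow. Prespecify a fallback to the centre-only model if the richer one does not converge. Settle this before the comparative results are seen.

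The cost is a change of wording and modest programming, with somewhat more work for the sparse binary outcomes. No new data are needed. Intervals become somewhat wider. In the 24-centre example (ICC 0.05, autocorrelation 0.8) the 95% half-width for LOS goes from 1.96 × 0.138 = 0.27 to 1.96 × 0.149 = 0.29 day, and power for 1 day stays above 99% under these assumptions.

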### Ethics and dissemination

The study protocol has been approved by the Ethical Committee of the coordinating Center and by all participating centers. The study is conducted under the regulations of the Declaration of Helsinki.

All information collected during the trial will be kept strictly confidential. Information will be held securely at the Clinical Epidemiology Unit, accordingly to all aspects of GDPR 2018. The trial staff at the participating centers will be responsible for ensuring that any data or documentation sent to the Clinical Epidemiology Unit is appropriately anonymized. At the end of the trial, data will be securely archived for a minimum of 20 years.

Study results will be timely circulated within the hospital network and published in peer-reviewed journals, reported in line with the literature Consolidated Standards of Reporting Trials guidelines for stepped wedge cluster randomized trials [18] and the RECOvER checklist [14].

### Trial status

The trial is currently adhering to V.2.0 of the protocol (approved in January 2020). Enrollment was initiated on the 1^st^ September 2019. Recruitment was initially expected to be completed in November 2020 but due to COVID outbreak is now expected to end in May 2021 (six months delay of the study timetable). At the beginning of May 2021 the number of patients enrolled is around 2400. Results will be available by the end of 2021.

## Discussion

This paper presents the study protocol of a stepped wedge cluster randomized controlled trial aimed to estimate the impact of a quality improvement intervention (the adoption of the ERAS protocol for hysterectomy in the entire regional hospital network in Piedmont). In 2017 an international survey [17] and a regional survey assessed that only few selected hospitals were compliant with the ERAS protocol in gynecologic surgery. Among the reasons for this limited uptake were the scarce diffusion of the multidisciplinary management of the patient and the lack of an organization that could enable the full adoption of the protocol, as a bundle, to obtain the desired positive effects.

To overcome the usual barriers to innovation in health care, especially at the organization level, and to monitor the changes in terms of appropriateness and safety, a structured Audit and Feedback (A&F) strategy has been planned in parallel to the trial. Even if the use of A&F is strongly recommended within the ERAS protocol, it is unusual that this strategy is carefully designed and conducted according to the best practice guidelines [21].

The “stepped wedge cluster randomized trial” study design has several advantages and some limits. Randomization at patient level would not be feasible due to the organizational nature of the intervention requiring a modification of the care process at center level. However, compared to other study designs, such as a before-after cluster randomized trial, the stepped wedge has a lower risk of bias due to possible confounding time effect and a complete coverage of the participating centers at the end of the study. This last advantage could theoretically represent even a risk in the unlikely, but not impossible, scenario of a disappointing effect of the experimental intervention.

Due to COVID-19 pandemic, the ERAS protocol was only partially implemented by some centers due to the shortage of staff and several organizational drawbacks. The extension of the study duration was intended to allow the centers, especially those in the third and fourth groups, to consolidate the implementation of the ERAS items. Such extension has also the purpose to get a sufficient sample size for the planned analyses on the secondary endpoints, counterbalancing the activity reduction (mainly among benign cases) registered during the pandemic.

To evaluate in a longer perspective both the effects and duration of the intervention and the impact of the COVID-19 pandemic, the time trend of some indicators (LOS, complications, readmissions) based on the routinely available data on hospital patient discharges will be analysed for the previous 5 years and monitored after study ending.

In conclusion, the main interest of the study results lies in the possibility to demonstrate positive clinical outcomes of the ERAS protocol even when its implementation is directed towards an entire regional network of gynecologic units, and not only towards selected and highly motivated ones. Moreover, the large cluster randomized trial reduces the risk of bias and the careful A&F strategy maximizes improvement of compliance. Due to these last aspects, the study will add useful evidence to the on-going EASY-NET project (http://easy-net.info/).
